#### **ix) Education and cost-effectiveness assessments**

Pre- and post-intervention education assessments will be performed in each school. This will involve a number of visits per year to each school. The first visit will occur one week prior to the biomedical assessments and will commence with classroom tests of attention for 30-60 minutes in standard 1 and individual assessments of pre-literacy and pre-numeracy skills. A team of 4 people can assess 60 children (2 classes) per day. With two survey teams, 10 schools can be surveyed per week and the pre-intervention surveys will be completed in all schools in 10-12 weeks. In the following term, the teams will return to conduct spot checks of attendance and to conduct classroom observations of pupil behavior and teaching methods. Two people can complete a school in one day and the assessment will take 5 weeks to complete. In the final term, the teams will return to conduct individual cognitive tests and detailed tests of literacy development. These tests will be on an individual basis and will take 4 testers 2 days to complete one school, taking around 15-20 weeks to complete.

Assessments will measure the foundational skills for literacy acquisition: specifically, letter knowledge, phonological awareness, print concepts, individual word reading, passage reading, and spelling. These foundational skills are recognized in the reading literature to be predictive of later reading acquisition in alphabetic languages. Furthermore, they are useful assessments because they are informative about a student's literacy knowledge and avoid floor effects. The assessments do not duplicate current MoE assessments. Instead, the current study will assess the literacy skills that are needed by a student if they are to meet the MoE goal that "the learners should acquire reading

skills to enable them to read and understand instructions, to read for information, and for pleasure (p. 55, Primary English Syllabus, 2002).

The method used to assess educational performance is appropriate for the local situation. People from the local community will be hired to serve as educational assessors. Since the assessments are administered individually, assessors will be trained to ensure children feel comfortable and can clarify the directions in the mother tongue. In addition, brief assessments are used in consideration of young children's attention spans.

The design of both literacy intervention and the assessment methods is the result of discussions with Ministry staff and other partners, including the Director of Primary Education, Kenya Ministry of Education, and Aga Khan Foundation and African Population and Health Research Centre (APHRC), who are developing literacy interventions for implementation in Coast Province.

The following educational assessments will be undertaken.

*School attendance:* Data on attendance over the year will be obtained from class attendance registers kept by teachers and which are completed daily as a routine. The registration system will be modified slightly to distinguish between absences due to illness (recorded as S) and those due to other causes (e.g. funerals, travel, home duties, recorded as O). Recording of absenteeism using the modified method will start three months prior to the intervention to establish the procedure in schools. Spot checks will be carried out for quality control. This method has worked successfully in other school health research projects in Kenya (Miguel & Kremer, 2003), although is invariably subject to reporting bias. Class attendance records will be collected at the end of each term for data entry.

*School performance:* In order to assess whether any improvements in attendance and attention result in increased learning at school, a test of school performance will be administered before treatment and at several subsequent points during the trial. School performance will be evaluated amongst all children in the study cohort, beginning in standard 1. We will assess all subjects but will focus particularly on the development of children's literacy and numeracy ([Appendix 4 and 5](#)). Recent evidence suggests that the Early Grade Reading Assessment (EGRA) is a cost-effective and simple means to assess children's literacy skills in the early grades (Jukes, Vagh, & Kim, 2006; RTI, 2008). Similar evaluation tools are available for early numeracy.

*Assessing mechanisms for the effect on improved school performance:* The impact of disease prevention on educational achievement happens through a number of different routes – more time spent in class, more time spent on-task whilst in class and improved cognitive abilities devoted to the task. The battery of behavioral assessments will be extended to capture full range of potential effects of the intervention ([Appendix 6](#)). A particular focus will be given to executive function tasks, such as sustained attention. These have been shown to be sensitive to the impact of malaria and anemia and are important for educational achievement in the early grades. Teams will also spend time in classrooms observing teacher and pupil behavior to assess how this changes in response to malaria intervention and teacher training (Jukes et al., 2006).

Tests will be conducted on the same day as, and immediately before, assessments of parasitaemia and anaemia. This will allow an analysis of the covariance between these biological indicators and ability to concentrate.

*Educational covariates:* Recent analyses of large school-based cluster controlled trials (Raudenbush et al., 2007) demonstrates that power can be increased considerably through the assessment of an extensive range of covariates, including teacher and school characteristics and classroom behavior. These will be assessed in the current study as part of the behavioural and educational assessment

battery. We will assess parental education and support for their children's education, teacher's levels of training, provision of textbooks, desks and other materials in the schools, and other socio-economic covariates ([Appendix 7](#)). A subset of families will be selected to conduct further interviews about how literacy development is supported in the home.

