**vii) Study interventions**

In this study, two interventions will be provided: i) intermittent screening and treatment (IST) for malaria and ii) a programme of training for primary school teachers to improve literacy instruction.

The malaria prevention strategy will involve all children being screened using rapid diagnostic tests (RDTs) for malaria once a term (thrice yearly). Children (with or without malaria symptoms) found

to be RDT-positive will be treated with artemisinin-based combination therapy (ACT). Screening and treatment will be administered by district health workers once a school term, observed by the evaluation research team.

An education intervention will be conducted in half of the schools receiving IST and half of the control schools. The intervention is designed to improved early grade literacy instruction. Recent evidence (Snow et al., 1998) suggests that relatively simple steps can be taken by teachers in order to improve the development of children's literacy in the early grades. It is particularly important to develop students' oral language skills (e.g., phonological awareness & vocabulary) and to teach the relationship between letters and sounds in a systematic and explicit fashion. Such instructional techniques are encouraged in the current Kenyan curriculum but teachers face many challenges in implementing them systematically and effectively. The aim of the instructional intervention will be to support teachers in implementing these teaching methods. Specific interventions will be design based on further consultation with all stakeholders and ongoing class observations in Kwale but may include training on (i) how to monitor students' progress in large classes (ii) developing and using instructional materials for reading (iii) lesson planning for explicit teaching of letter-sound relationships (iv) instructional techniques for large classes.

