### **xiii) Local Safety Monitor (LSM)**

The overall role of the Local Safety Monitors (LSM), who are experienced clinicians based in-country and based in Kilifi or Nairobi, will be to support the clinical investigators and to act as a link between the investigators and the DSMB. The LSM's role will include:

- Acting as the study volunteer's advocate.
- Promptly communicating relevant safety information to the DSMB.
- Providing advice to the investigators on whether a set of clinical circumstances in a study warrants formal notification to the DSMB.
- Conduct a site visit to investigate every report of a SAE
- Unblinding a subject if deemed necessary to allow for adequate treatment.
- Liaising closely with the chair of the DSMB throughout the course of the trial.

The relevant LSM will be informed by the investigator on an 'as received' basis of:

- All SAEs.
- All withdrawals of study subjects by the Principal Investigator or the parent(s)/ guardian(s) of a subject due to adverse events.

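### The survey teams that observe teaching also give the later one-to-one literacy tests, and nothing keeps testers unaware of a school's literacy allocation

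*Protocol*

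**What the plan says.** Protocol section 8 ii makes education achievement, covering reading, writing and arithmetic, the second primary outcome. Section 8 ix sets out who collects the education data and when:

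- **Workforce.** "A team of 4 people can assess 60 children (2 classes) per day", and "With two survey teams, 10 schools can be surveyed per week". Two teams of four make eight people.
- **Next term.** Here "the teams will return to conduct spot checks of attendance and to conduct classroom observations of pupil behavior and teaching methods". Two people finish a school in a day, and the round takes 5 weeks.
- **Final term.** "In the final term, the teams will return to conduct individual cognitive tests and detailed tests of literacy development". These tests are individual, need four testers for two days per school, and take 15 to 20 weeks.
- **Latitude.** In the individual tests, "assessors will be trained to ensure children feel comfortable and can clarify the directions in the mother tongue".

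The part of section 8 ix on mechanisms says classroom observation is meant to show how teachers and pupils respond to the malaria intervention and to teacher training. The part on classroom visits adds repeated observation of each teacher, an instrument that records literacy teaching methods, and an interview of about 30 minutes between observer and teacher. Section 8 vii describes the literacy intervention as a change in how teachers teach oral language and letter-sound relationships.

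The protocol does not say that education testers are kept unaware of allocation, that observers and testers are different people, or that teams change schools between rounds.

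**The concern.** The literacy intervention cannot be hidden from someone who watches the lessons, since changed teaching is what the observation is designed to record. If the observer later sits with the pupils of that school and gives the tests, the score is collected by someone who probably knows the allocation. One-to-one testing with permission to clarify directions leaves room for small, unintended differences in explanation, encouragement or scoring.

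A difference of that kind that follows the allocation enters the school means directly and looks like an effect of the literacy programme. Adding schools or children does not shrink it, and an analysis cannot remove it afterwards, because it cannot be told apart from a true effect. The target effect is only 0.2 SD, so a modest shift matters.

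**Working it through.** **1. Do the stated durations leave room for a separate observer group?**

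Inputs: two teams of four, the stated pace and durations (section 8 ix), and 100 schools (sections 8 v and 15). Assumption: a five-day week.

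| Round | Calculation | Result | Protocol |
|---|---|---|---|
| First visit | 100 schools / 10 per week | 10 weeks | 10–12 weeks |
| Observation | 8 people / 2 = 4 pairs; 4 × 5 days = 20 schools per week; 100 / 20 | 5 weeks | 5 weeks |
| Individual tests | 2 teams × 5 days / 2 days = 5 schools per week; 100 / 5 | 20 weeks | 15–20 weeks |

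One pair would need 100 / 5 = 20 weeks for the observation round, and two pairs 10 weeks. Only four pairs, which is all eight people, meet the 5 weeks. Testing in 20 weeks needs 100 × 4 × 2 / (20 × 5) = 8 testers. Testing in 15 weeks would need 800 / 75, or about 10.7. The durations therefore fit the same eight people doing both jobs. The shorter end of the testing range would need a few more people, whom the protocol does not mention.

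**2. How large could the consequence be?**

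Inputs from section 8 v: 50 children per school, ICC 0.2, correlation 0.7 between baseline and final scores. Section 15 puts the literacy intervention in 50 of the 100 schools, so the comparison is 50 against 50.

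- Variance of a school mean: 0.2 + 0.8/50 = 0.216 (SD units).
- After baseline adjustment: 0.216 × (1 − 0.7²) = 0.216 × 0.51 = 0.110. This assumes that the 0.7 also holds for school means.
- SE = √(2 × 0.110 / 50) = 0.066 SD.
- Check against the plan: (1.96 + 0.84) × 0.0664 = 0.186 SD is detectable with 80% power, and power at 0.2 SD is about 85%. This agrees with the protocol's 0.2 SD target.

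With no true effect and an assessor shift b, the two-sided 5% test rejects with probability Φ(b/SE − 1.96) + Φ(−b/SE − 1.96):

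| Assumed shift b | b/SE | Rejection rate |
|---|---|---|
| 0.02 SD | 0.30 | about 6% |
| 0.05 SD | 0.75 | about 12% |
| 0.10 SD | 1.51 | about 33% |

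Without baseline adjustment, SE = √(2 × 0.216 / 50) = 0.093 SD, and shifts of 0.05 and 0.10 SD give about 8% and 19%. The documents supply no value for b; these are chosen only to show the scale.

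**3. Does a crossover fit the timetable?**

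If each team observes 50 schools, its two pairs cover 10 schools per week, which takes 5 weeks. If each team tests the other 50, at two days each, that is 100 working days, or 20 weeks. Both durations are unchanged.

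**The case against.** The strongest reply is that the protocol never claims masked education assessors, so the schedule removes nothing. It also speaks of the teams collectively and never assigns a team to a school, so a crossover is already compatible with the text, and field procedures could provide it. The staffing arithmetic shows overlap of the workforce, not of person and school. All of this stands, and it limits the point to an exposure that the plan permits and does nothing to prevent.

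Three further replies stand in part:

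- **Which round supplies the endpoint.** The final-term visit covers cognitive and literacy tests and does not mention arithmetic. Section 8 viii has two education testers assess achievement in the week before the health team, and section 8 ix foresees several test points. The endpoint round is not stated, but no round has masked testers.
- **Latitude.** Clarifying directions is not prompting answers, and the instruments are in appendices that are not shown, so a script may exist.
- **Size.** The assumed shifts have no basis in the documents, and at 0.02 SD the inflation is slight.

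A reader might also infer more than the documents support:

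- **IST allocation.** "Screening and treatment will be administered by district health workers once a school term, observed by the evaluation research team" does not say that education testers are among those observers, and section 8 viii lists the testers apart from the health team. The stated aim of watching responses to the malaria intervention is only a weak pointer.
- **Local hiring.** "People from the local community will be hired to serve as educational assessors" does not place assessors at schools in their own community.
- **Placebo.** It cannot be said flatly that masked testing is the only protection left. Sections 6, 8 v and 15 mention placebo and section 8 vi mentions coded drug groups, while sections 8 i and 8 vii describe controls receiving neither intervention.
- **Safety monitor.** "Unblinding a subject if deemed necessary to allow for adequate treatment" concerns clinical care of a participant and implies nothing about education testers.
- **Haemoglobin and blood slides.** Nothing here shows a defect in how they are read.

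**Conclusion.** The point holds as a design weakness that should be corrected before post-intervention testing begins. Section 8 ix gives one workforce both the observation of teaching and the individual literacy testing, its durations fit all eight people in both rounds, and nothing separates the roles or keeps testers unaware of allocation. Followed as written, the plan allows a tester to know a school's literacy allocation while collecting data for a primary outcome.

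It should not be read as a breach of declared masking, or as proof that any individual tests a school he or she observed. The exposure is shown for the literacy comparison; for IST it remains conjecture.

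The consequence could run from negligible (about 6% error at a 0.02 SD shift) to serious (about 33% at 0.10 SD, half the target effect). Those figures rest on the section 8 v inputs, a normal approximation, baseline adjustment that works at school level, and assumed shifts. The point does not depend on an analysis plan, because it concerns who collects the data.

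**What to change.** In Protocol section 8 ix:

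1. Cross over the two teams, so that nobody tests pupils after baseline at a school where they have observed teaching or interviewed teachers.
2. Spread each team's test schools over all four arms, so that differences between testers do not line up with allocation. Someone who holds the allocation list, and does not test, should draw the roster.
3. State that testers are not told allocation and do not attend IST rounds at schools they test. The IST part is a precaution.
4. Use scripted mother-tongue directions in place of free clarification, or say so if the appendices already contain them.

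This costs protocol and field-manual wording, a redrawn roster, some extra travel, and the loss of a team's familiarity with a school. It needs no extra staff or visits. The crossover reduces exposure but cannot guarantee masking: a tester who spends two days in a trained school may still recognise it, and team members may talk.

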#### *Classroom Visits:*

The evaluation is interested in differences between teachers' instructional behaviors that lead to better reading outcomes. With the teacher's permission, we will video their classroom instruction while simultaneously observing. Each teacher will be observed several times with two instruments. The Stalling (Stallings, 1980) instrument codes the activities engaged in and materials used at multiple time points within one class period. The second instrument, the CLASSIC (Scanlon et al., 2003), assesses specific methods for literacy instruction. Following the lesson, the observer will meet with the teacher for about 30 minutes for a structured interview. The observations, videos, and interviews will support a more detailed analysis of how teachers' behaviors differ and help our understanding of the ways teachers can influence their pupils' reading acquisition.

*Cost benefit and effectiveness analysis:* The evaluation will also examine the costs, cost-benefits and cost-effectiveness of IST in improving educational and health outcomes. The costs of IST will be assessed from both a provider's and societal perspective. Both financial and opportunity costs will be evaluated using standardized methodologies (Drummond et al., 2005). In addition to estimating the rate of return to education, cost-benefit analysis will incorporate improved cognition and learning into the benefit streams (Jimenez & Patrinos, 2008). A comparison of and benefits of other education interventions in Kenya (e.g. Miguel & Kremer, 2004; Glewwe et al., 2004; Glewwe & Kremer, 2006) will also be undertaken. Cost per case of anaemia will also be assessed.

*Process evaluation:* This will aim to (i) investigate community acceptability of malaria intermittent screening and treatment; and (ii) document factors external to the intervention which might impact upon both its implementation and its effectiveness. Such an evaluation will help the interpretation of results and help inform future large-scale implementation of the intervention.

First, a modified stakeholder analysis approach will be adopted to identify and assess the importance of key people, or groups of people who are likely to affect the implementation and longer-term sustainability of the programme (Steckler & Linnan, 2004; Varvasovszky & Brugha, 2000). Key stakeholders are likely to include: teachers, parents, children, community leaders, local health workers and education officers as well as individuals at provincial and central levels in the Ministries of Education and Health. Stakeholders from both intervention and control schools will be included in order to obtain views on the intervention, but also the acceptability of not immediately receiving the intervention. An assessment will be made of their importance to the success and sustainability of the programme and data on their views about the programme (e.g., expectations of the intervention, experiences of the intervention, acceptability of the approach, value to individuals & communities, impact on workload) will be collected through a series of focus group discussions as well as semi-structured interviews with people identified as key informants (Bernard, 2006). Discussions and interviews will be transcribed and translated, and content analysis using Nvivo 8 (QSR International, Melbourne, Australia) will be undertaken to identify themes based on people's experience and involvement in the intervention.

Second, an analysis will be undertaken of the structural, organisational and management factors that enhance or constrain effective implementation of this and other school-based screening and treatment programs, for example, deworming and vitamin A, by staff from the Ministries of Health and Education. In addition to identifying and mapping these stakeholders through the stakeholder analysis, interviews will be conducted with purposefully selected key stakeholders in order to assess the organization and managerial capacities of the government at national and local levels (Jones et al., 2008). These data will be analysed and interpreted iteratively based on implementation and

organizational management theories (Damschroder et al. 2009) and the developed stakeholder analysis framework.

**x) Laboratory procedures**

Thick and thin blood smears will be stained with 2% Giemsa for 30 minutes and read by experienced laboratory technicians. Parasite densities will be calculated by counting the number of asexual parasites per 200 leukocytes (or per 500 leukocytes, if the count is <10 asexual parasites/200 leukocytes), assuming a leukocyte count of 8000/ $\mu$ l. A blood smear will be considered negative when the examination of 200 high power fields does not reveal asexual parasites. Thin smears will also be made for counting high parasitaemias. For quality control, all slides will be read by a second microscopist and a third reviewer will settle any discrepant readings.

Haemoglobin levels will be measured using a portable HemoCue photometer (HemoCue, Angelhom, Sweden).

Stool examinations will be conducted to determine the prevalence and intensity of intestinal nematodes, using the Kato-Katz method. Urine examinations will also be conducted to determine the prevalence and intensity of *Schistosoma haematobium*, using the urine filtration method.

